**2. Recruitment and retention**	Can we recruit, train, and retain enough PLWP to be SCAPE-U facilitators? Can we recruit and retain sufficient primary care workers, community health workers and service users and their caregivers for outcome assessment?	PLWP can be adequately recruited, trained, and retained for delivering the SCAPE-U intervention For primary care workers, community health workers and service users and their families, maximum recruitment might be required to address loss to follow-up and drop-out	Process output: number of SCAPE-U facilitator recruited, completed training, and retained. Target = 50% retention For primary care workers, community health workers: number in health posts, number completing the training, supervision and completing outcome measures. Target for both = 60% at 8 months follow-up For SU and families: 50% completing the 5 session home visits	SCAPE-U facilitators, primary care workers, community health workers, service users and their families, research staffs
**3. Acceptability and feasibility measures and data collection procedures**	Are the quantitative and qualitative assessment measures and collection procedure acceptable and feasible to administer with the stakeholders at planned intervals?	The selected measures will be acceptable and feasible for measuring the intended outputs of the study	Tool completion rate, time, missingness of data (target: fewer than 20%)	Primary care workers, community health workers, service users and families, research staff
**4. Randomization**	Is cRCT feasible to run the study and measure the intended outcomes—in terms of contamination, fidelity, and implementation strategy?	Cluster randomization is feasible to execute the study and measure intended outcomes	Baseline summary of two arms Demographic details of primary care workers, community health workers (age, gender, years of experience, qualifications, education) Record on participant’s arm crossover (target: less than 30%)	Primary care workers, community health workers, service users and families, research staff

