### Study participants

This study will involve six categories of study participants:(i)People with lived experience of psychosis trained as SCAPE-U facilitators—8 to 10 people with lived experience of psychosis who have previously received services from YouBelong Uganda [33, 35] will be recruited. The inclusion criteria are (1) diagnosis of a psychotic disorder confirmed by a mental health professional (psychiatric clinical officer or psychiatrist). (2) Capacity to provide informed consent. The main exclusion criterion is any health, functional, or cognitive impairment, assessed through mental state examination, that could jeopardize their full and safe participation in SCAPE-U activities. There are no inclusion/exclusion criteria relating to current engagement in treatment.(ii)Primary care workers—two primary care workers will be selected per health facility, with a target of 36 primary care workers per arm (72 total for the study). There are no exclusion criteria.(iii)Community health workers—we will select up to five community health workers from each health facility. This will equate to approximately 90 community health workers per arm and an estimated total of 180 community health workers for the study.(iv)Psychiatrists, psychiatric clinical officers,and psychiatric nurses—1 psychiatrist, 3 psychiatric clinical officers, and 2 psychiatric nurses who are involved in delivering training to primary care workers will be included.(v)Service users diagnosed with psychosis by primary care workers—the primary intended beneficiaries of study interventions are service users receiving treatment for psychosis at primary care facilities. The goal is to have 10 service users per cluster, 30 per arm, and 60 in total for the study. *Inclusion criteria*: (1) persons diagnosed with psychosis at a primary health care facility in Kampala/Wakiso District, following mhGAP training as part of the SCAPE-U trial; (2) ability of the service users to consent to study enrollment and procedures, or, if the service user does not have capacity to consent, a responsible surrogate can give consent; (3) persons eligible for outpatient management of psychosis. *Exclusion criteria*: (1) persons diagnosed with psychosis requiring inpatient management; and (2) persons for whom consent for participation in the study cannot be obtained.(vi)Family members of service users—at least one primary carer for study service users will be identified to collect outcome data from a family perspective (*n* = 30 per arm, 60 for the total study).

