### Measures/outcomes for feasibility criteria and other objectives

The primary outcome of this trial is to understand the feasibility and acceptability of the SCAPE-U intervention. We have developed a set of quantitative and qualitative measures to do this as guided by recommendations from pilot study reporting [49]. These measures will determine what components of the SCAPE-U intervention will be included, excluded, or modified in the future full trial. The following quantitative criteria have been set to determine if this feasibility trial can be scaled up for a fully powered trial.Recruitment: at least 2 primary care workers were recruited in the study from each of the 36 health facilities selected.Retention: 50% of SCAPE-U facilitators retained by the end of PhotoVoice training, 60% of primary care workers, 60% of community health workers retained in post until the end of the 8 months follow-up period, and 50% of service users and families retained by the end of 5 session home visits.Contamination: less than 20% of cross-arm movement of primary care workers, community health workers, service users, and their families during the 8-month follow-up period.Cluster comparison: measuring baseline characteristics of recruited primary care and community health workers across both arms. We will collect information on primary care workers and community health workers’ education qualifications, gender, prior mental health training, age, and years of experience and determine balance between arms.Data collection procedure: less than 20% of missingness in collected data.Safety: fewer than 20% of adverse events among recruited SCAPE-U facilitators and service users.

Our qualitative criteria for this feasibility study are presented in Table 3.

**Table 3 Tab3:** Assessment of feasibility and acceptability of the intervention and trial procedures

Domains	Research questions	Methods
Feasibility and acceptability of SCAPE-U intervention	Do psychiatrist/psychiatric clinical officer, primary care workers, and mental health service users find it feasible and acceptable for PhotoVoice trained people with lived experience to participate as co-facilitators in training and supervision?	● Qualitative interviews with psychiatrist/psychiatric clinical officer, primary care workers, SCAPE-U facilitators, and research staff ● Process notes from trainings and supervision sessions

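### The limit for cross-arm movement is below 20% in the scale-up criteria and below 30% in Table 1, so one observed rate can fail one pre-specified rule and pass the other

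*Protocol article*

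**What the plan says.** Under Measures/outcomes for feasibility criteria and other objectives, the protocol article introduces its list this way: "The following quantitative criteria have been set to determine if this feasibility trial can be scaled up for a fully powered trial". The contamination item in that list sets the limit at "less than 20% of cross-arm movement of primary care workers, community health workers, service users, and their families", counted over the 8 months of follow-up.

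Table 1, under Objectives, has a row for objective 4, Randomization. Its research question is whether a cluster randomized trial is feasible "in terms of contamination, fidelity, and implementation strategy". Its methods cell includes a record of "arm crossover (target: less than 30" per cent). The participants column names the same four groups as the criteria list and adds research staff.

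The planned sizes are under Study participants. Primary care workers are planned "with a target of 36 primary care workers per arm (72 total for the study"), and community health workers as "an estimated total of 180 community health workers for the study". Service users number 60 in total, and so do family members.

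**The concern.** Two pre-specified limits are set for one quantity, and they differ by ten percentage points. Feasibility is the trial's primary purpose, and under Sample size the article rules out a power calculation and formal hypothesis testing. The quantitative criteria are therefore the numerical rules by which the pilot is read.

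If observed movement falls between the two limits, the contamination result has no single reading. The team could report it against either figure, and that choice could be made with the data in hand. Movement is a real prospect in this setting: Study design itself anticipates that health workers may be transferred by the government.

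**Working it through.** **1. Is it the same quantity?** The criteria list defines contamination as movement between arms. The Table 1 row asks about contamination and measures it by arm crossover in the same groups. One difference is that the list fixes the window ("during the 8-month follow-up period") and the Table 1 row gives none. This does not separate the two measures, because the Table 1 row names no other window.

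**2. Could the wording explain the gap?** Table 1 speaks of a target and the list of criteria. Table 1 uses the word target for other limits too, and their percentages agree with the list:

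| Limit | Table 1 | Criteria list |
|---|---|---|
| Missing data | below 20% | below 20% |
| Adverse events | below 20% | below 20% |
| Retention, SCAPE-U facilitators | 50% | 50% |
| Retention, primary care and community health workers | 60% | 60% |
| Retention, service users and families | 50% | 50% |
| **Cross-arm movement** | **below 30%** | **below 20%** |

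Of these shared percentages, only cross-arm movement differs. No passage describes a traffic-light scheme or separate target and stop limits. Neither figure has a derivation in the article, so there is no calculation to reproduce.

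**3. Which counts are affected?** With n people, a count x fails the 20% rule when x ≥ 0.20n and passes the 30% rule when x < 0.30n. The conflict zone is every whole number that meets both conditions.

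| Group | n | 0.20n | 0.30n | Fails the list, passes Table 1 |
|---|---|---|---|---|
| Primary care workers | 72 | 14.4 | 21.6 | 15–21 |
| Community health workers | 180 | 36 | 54 | 36–53 |
| Service users | 60 | 12 | 18 | 12–17 |
| Family members | 60 | 12 | 18 | 12–17 |
| All four pooled | 372 | 74.4 | 111.6 | 75–111 |

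**4. How likely is a result in that zone?** The documents give no expected rate of movement, so this step is illustrative only. Take a true rate p and treat movements as independent, which ignores clustering. The probability of a contradictory result is then P(a ≤ X ≤ b), with X binomial(n, p) and a to b the zone above.

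| True rate p (assumed) | Primary care workers | Community health workers | Service users |
|---|---|---|---|
| 15% | 11% | 4% | 18% |
| 20% | 45% | 53% | 51% |
| 25% | 66% | 88% | 63% |
| 30% | 47% | 47% | 42% |

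The finding does not depend on these probabilities. It rests on steps 1 to 3.

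**The case against.** The strongest reply is that little hangs on the discrepancy. Contamination is one of six criteria. The same section says the measures will guide which components are kept, dropped or changed. The Discussion says that problems will lead to modification and, where significant changes are needed, to consideration of an internal pilot within the full trial. A rate of 20% to below 30% would therefore not clearly stop anything. This stands as a limit on the consequence. It does not remove the contradiction, because the list is still said to determine whether the trial can be scaled up.

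Some stronger readings are tempting, and the documents do not support them:

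- **That this number decides whether the cluster design is kept.** Study design says individuals cannot be randomized because the interventions work at facility and community level. No individually randomized fallback depends on the threshold. Objective 4 also covers fidelity, implementation strategy and a baseline comparison of the arms.
- **That the two limits translate into a sample-size penalty for the full trial.** If a fraction c of control participants received the intervention, the sample size would grow by 1/(1−c)²: 1/0.8² = 1.56 at 20% and 1/0.7² = 2.04 at 30%. The criterion does not measure c. It counts movement in any of four groups and in either direction, and the article gives no link from movement to exposure. At 20% movement the factor could be 1.0 if no mover's exposure changed, or 1/(1−0.4)² = 2.78 if 20% in each arm fully exchanged exposure. No multiplier follows from the text.
- **That the absence of a per-group or pooled rule is a further error.** A condensed article may leave that detail to the full protocol or analysis plan, neither of which is shown. The 20% versus 30% conflict exists under either rule.

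**Conclusion.** The contradiction holds. Any observed rate of at least 20% and below 30% fails the criteria list and passes Table 1; below 20% or from 30% upwards the two rules agree. The counts assume that planned recruitment is met. With fewer recruits they change, but the percentage range does not.

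A reader might infer that the stricter 20% is the intended or safer figure. The documents give no basis for that: neither number is justified, and nothing shows which is the slip. The conclusion is limited to a pre-specified progression criterion that cannot be applied unambiguously as written. Allocation and estimation of outcomes are not affected.

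**What to change.** Before any crossover data are reviewed, reconcile Table 1, objective 4, with the contamination item in the criteria list, and state one threshold in both places. The sponsor has to say which figure was meant. If two bands were intended, the article should say so and give the action attached to each.

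The cost is one corrected number. If 20% is kept, the criterion is slightly harder to meet: at planned sizes the largest passing counts are 14 of 72 primary care workers, 35 of 180 community health workers, and 11 of 60 service users or family members. At 30% they are 21, 53 and 17.

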## Objectives

This current protocol describes a feasibility study using a cluster randomized controlled trial (c-RCT) design. The pilot study compares implementation as usual for mental health services to the SCAPE-U implementation strategy, in which PWLP collaborates in training primary care workers and community health workers, as well as conducting home visits to service users and their families. The pilot and feasibility study have the following objectives (see Table 1):To assess the feasibility and acceptability of involving people with lived experience of psychosis in mental health trainings and home visits.To determine recruitment and retention rates of SCAPE-U facilitators, service users and their caregivers, primary care workers, and community health workers.To establish the acceptability and feasibility of data collection procedures.To demonstrate the feasibility of trial procedures.To demonstrate the ethics and safety of the study procedures.To describe changes in outcome measures at individual, family, and health system levels.To determine the cost of the SCAPE-U implementation strategy.

**Table 1 Tab1:** Feasibility trial objectives

**Objective**	**Resear**ch questions	**Hypothesis**	**Methods**	**Participants**
**1. Feasibility and acceptability of SCAPE-U**	Is it feasible to train and involve people with lived experience of psychosis in the intervention? Do primary care workers, community health workers and caregivers of service users find it acceptable to have people with lived experience of psychosis as co-facilitators in their trainings/supervision and home visits?	People with lived experience of psychosis can be trained to deliver training and home visits effectively and safely All the key stakeholders of the intervention will find the involvement of people with lived experience acceptable	Qualitative interviews Process notes Adverse event logs (target: fewer than 20% among recruited PWLE)	SCAPE-U facilitators, primary care workers, community health workers, service users and their families, research staff and trainers

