### Study design

The design is a cluster-randomized controlled feasibility trial comparing the standard implementation arm, where PCWs will be trained by mental health specialists, versus the intervention arm, where, in addition, PWLP will cofacilitate the PCWs training and provide home visits to the service users with psychosis.

The unit of randomization is a geographic cluster of primary care facilities. There are 36 primary care facilities in the two study districts. These will be divided into six geographic clusters based on a health subdistrict, each consisting of six primary care facilities. Three geographic clusters will be randomly allocated to the control arm and three to the SCAPE-U arm. We chose a cluster design because the interventions are delivered at a primary care facility and community level, meaning individual randomization is not possible. Having multiple health workers and primary care facilities in each cluster also ensures that we will not lose the entire cluster in the scenario that primary care workers or community health workers retire or are relocated by the government.

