### Home level

Service users receiving service from the health facilities in the control arm will not receive any additional service besides that provided from health facilities. For those receiving service from the intervention arm and diagnosed with psychosis, SCAPE-U facilitators will conduct five 1-h home visits to service users who have been diagnosed with psychosis by primary care workers and are currently receiving treatment. Primary caregivers to service users are expected to be present during these visits. Each session will consist of SCAPE-U facilitators sharing their lived experiences through a 10-min presentation of an aspect of their PhotoVoice story. Each session will be tailored to a psychosocial theme (medication adherence, conflict resolution, stigma, livelihood support, and dealing with challenging behaviors) [33, 35]. There will then be time for questions and discussion with the service users and their family (Table 2).

**Table 2 Tab2:** Overview of services and implementation by study arm and level of care

Care level	Standard services arm	SCAPE-U arm
Primary care	mhGAP-IG training conducted by a psychiatrist and/or psychiatric clinical officer for 5 days with a focus on psychosis diagnosis and treatment	mhGAP-IG training conducted by a psychiatrist or psychiatric clinical officer combined with a SCAPE-U facilitator (people with lived experience of psychosis) presenting recovery stories and other activities
Community	2-day training conducted by trained psychiatric clinical officer or psychiatric nurse on identification and referrals of people potentially experiencing psychosis	2-day training conducted by trained psychiatric clinical officer or psychiatric nurse, combined with SCAPE-U facilitator presenting recovery stories and other activities
Home	No services	5 fortnightly sessions of psychosocial support provided by SCAPE-U facilitators using PhotoVoice narratives based on themes in the YouBelongHOME intervention

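### The 20% safety criterion is stated with two different denominators, so the number of affected people it tolerates ranges from 1 to 13 depending on the reading

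*Protocol article*

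**What the plan says.** The protocol article gives the 20% adverse-event limit in two places.

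- **Measures/outcomes for feasibility criteria and other objectives.** The list opens with its purpose: "The following quantitative criteria have been set to determine if this feasibility trial can be scaled up for a fully powered trial". Its last item reads: "Safety: fewer than 20% of adverse events among recruited SCAPE-U facilitators and service users".
- **Objectives, Table 1, objective 1.** The methods column reads: "Adverse event logs (target: fewer than 20% among recruited PWLE". This objective concerns involving people with lived experience in training and home visits.

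The group sizes come from Study participants. For facilitators: "8 to 10 people with lived experience of psychosis who have previously received services from YouBelong Uganda". For service users: "The goal is to have 10 service users per cluster, 30 per arm, and 60 in total for the study". Allocation is in Study design: "Three geographic clusters will be randomly allocated to the control arm and three to the SCAPE-U arm".

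Facilitators work only in the intervention arm (Randomization and blinding). The Home level section states for controls: "Service users receiving service from the health facilities in the control arm will not receive any additional service besides that provided from health facilities". The Abstract counts the safety of collaborating with people with lived experience of psychosis among the primary outcomes.

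**The concern.** One numerical limit is attached to two differently described groups. In Table 1 the context points to the facilitators. The progression list adds service users, a much larger group, half of whom are planned for the control arm and have no contact with facilitators through the trial. The text does not say whether the groups are summed or judged one by one, whether both arms count, or whether the numerator is people or events. Read literally, a percentage of adverse events is not a proportion of either group.

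This limit is one of the listed criteria for moving to a full trial, and it bears on an outcome that the Abstract calls primary. If the same data can pass under one statement and fail under the other, the safety judgement could be settled after the results are known, by choosing a denominator.

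**Working it through.** **Inputs.** Facilitators F = 8, 9 or 10 and service users S = 60, or 30 per arm (Study participants). Threshold: strictly below 20% (both places).

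**The plan's own figures.** 10 service users per cluster × 6 clusters = 60, and 10 × 3 = 30 per arm. Both match. The 20% is given without derivation, so there is nothing to reproduce for it.

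**Assumption.** The unit is a person with at least one adverse event, because the text does not state a unit.

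**Step 1: largest number of affected people that still meets the criterion.** This is the largest integer k with k/N < 0.20.

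| Denominator | N | Largest k that passes | Next k fails |
|---|---|---|---|
| Facilitators only | 8 | 1 (12.5%) | 2/8 = 25.0% |
| | 9 | 1 (11.1%) | 2/9 = 22.2% |
| | 10 | 1 (10.0%) | 2/10 = 20.0% |
| Facilitators + 30 intervention-arm service users | 38 | 7 (18.4%) | 8/38 = 21.1% |
| | 39 | 7 (17.9%) | 8/39 = 20.5% |
| | 40 | 7 (17.5%) | 8/40 = 20.0% |
| Facilitators + all 60 service users | 68 | 13 (19.1%) | 14/68 = 20.6% |
| | 69 | 13 (18.8%) | 14/69 = 20.3% |
| | 70 | 13 (18.6%) | 14/70 = 20.0% |

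An exact 20.0% fails because the limit is strict. Service users judged alone would allow 5 of 30 (6/30 = 20.0% fails) or 11 of 60 (12/60 = 20.0% fails).

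**Step 2: every facilitator affected.** The pooled share is F/(F + S) when no service user is affected.

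- S = 60: 8/68 = 11.8%, 9/69 = 13.0%, 10/70 = 14.3%. All pass. The room left for affected service users is 13 − 8 = 5, 13 − 9 = 4 and 13 − 10 = 3.
- S = 30: 8/38 = 21.1%, 9/39 = 23.1%, 10/40 = 25.0%. All fail. However, 7 affected facilitators would still pass if no service user were affected.
- Facilitators judged alone: 100%, a clear fail.

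**Step 3: one data set, opposite answers.** Take 3 of 10 facilitators affected and no service users. On the facilitator reading of Table 1, 3/10 = 30%, a fail. Pooled over both arms, 3/70 = 4.3%, a pass. Pooled with the intervention arm only, 3/40 = 7.5%, also a pass.

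**Step 4: the opposite direction.** Suppose 14 control-arm service users are affected and nobody else. Pooled over both arms, 14/70 = 20.0%, a fail, although no facilitator and no visited service user had an event.

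**The case against.** A reader might infer something stronger: that the progression criterion is satisfied whatever happens to the facilitators, and so hides the harm the trial is meant to detect. The documents do not support that, for these reasons.

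- **Pooling is one reading only.** The sentence names two groups and does not say they are added. The contamination item in the same list sets one limit for four populations, where a per-group reading is natural. Judged per group, 10 of 10 facilitators is a fail.
- **The arm is unstated.** In the retention item of the same list, "50% of service users and families retained by the end of 5 session home visits" can only refer to the intervention arm, since controls receive no home visits. If the safety item means the same 30 people, the result for all facilitators affected reverses to a fail.
- **Even over 60 service users the pass is conditional.** It needs at most 3 to 5 of them to be affected.
- **The unit is open.** It would be too strong to say that the numerator is definitely events. If events are counted, repeat events could breach 20% on their own.
- **Both targets might be meant to apply.** Table 1 places its figure under objective 1, while ethics and safety is objective 5, which has no figure. PWLE is also formally wider than the facilitators and could take in service users.
- **Facilitator harm is watched in other ways.** There is a collaboration checklist at several points, interviews with 75% of the facilitators who completed training and delivery, an adverse event log and an independent monitoring board. The Discussion also foresees modification or an internal pilot, so this percentage is not the only route to a decision.

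All of this stands against the stronger claim. It does not remove the inconsistency: each alternative is a further possible denominator or unit, and the document does not choose among them. Nor is this detail that an article may leave to a fuller document, because the two differing statements are both printed here. The definition of a qualifying event is different: it may sit in the monitoring board protocol or operating procedures, and its absence is not held against the plan.

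**Conclusion.** The point holds as an inconsistency in a progression criterion. The limit is worded for two different groups, and pooling, arm and counting unit are unstated. Counting persons, and with the planned numbers recruited, the number who may be affected with the criterion still met is 1, 7 or 13 across the three denominators. The same data can fail at 30% and pass at 4.3%. That the criterion can be met with every facilitator affected is true only if groups are pooled over both arms, persons are counted, and no more than 5 to 3 service users are affected (for 8 to 10 facilitators). It is not true if only the intervention arm is pooled or if groups are judged separately. Reading PWLE in Table 1 as the facilitators rests on context, not on the abbreviation list. Because the choice can change the progression decision on an outcome the Abstract names as primary, this is more than a missing detail.

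**What to change.** Reconcile Table 1 (objective 1) and the progression list to a single definition before results are known:

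- the measure is the proportion of persons with at least one adverse event;
- it is judged separately for facilitators and for intervention-arm service users;
- control-arm service users are reported alongside as the reference;
- the groups are not pooled.

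Which events qualify is for the sponsor to define, and the definition should be the same in both places.

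The cost is wording in two places. The adverse event log and the arm allocation should be enough for the count, provided that the log identifies the person; the article does not describe its fields. The criterion becomes stricter for facilitators than under the pooled reading: with 8 to 10 of them, at most one may be affected. For intervention-arm service users the limit would be 5 of 30.
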